## Abstract

**Background:**

Arterial carbon dioxide tension (PaCO_2_), oxygen tension (PaO_2_), and mean arterial pressure (MAP) are modifiable factors that affect cerebral blood flow (CBF), cerebral oxygen delivery, and potentially the course of brain injury after cardiac arrest. No evidence regarding optimal treatment targets exists.

**Methods:**

The Carbon dioxide, Oxygen, and Mean arterial pressure After Cardiac Arrest and REsuscitation (COMACARE) trial is a pilot multi-center randomized controlled trial (RCT) assessing the feasibility of targeting low- or high-normal PaCO_2_, PaO_2_, and MAP in comatose, mechanically ventilated patients after out-of-hospital cardiac arrest (OHCA), as well as its effect on brain injury markers. Using a 2^3^ factorial design, participants are randomized upon admission to an intensive care unit into one of eight groups with various combinations of PaCO_2_, PaO_2_, and MAP target levels for 36 h after admission.

The primary outcome is neuron-specific enolase (NSE) serum concentration at 48 h after cardiac arrest. The main feasibility outcome is the between-group differences in PaCO2, PaO2, and MAP during the 36 h after ICU admission. Secondary outcomes include serum concentrations of NSE, S100 protein, and cardiac troponin at 24, 48, and 72 h after cardiac arrest; cerebral oxygenation, measured with near-infrared spectroscopy (NIRS); potential differences in epileptic activity, monitored via continuous electroencephalogram (EEG); and neurological outcomes at six months after cardiac arrest.

**Discussion:**

The trial began in March 2016 and participant recruitment has begun in all seven study sites as of March 2017. Currently, 115 of the total of 120 patients have been included. When completed, the results of this trial will provide preliminary clinical evidence regarding the feasibility of targeting low- or high-normal PaCO_2_, PaO_2_, and MAP values and its effect on developing brain injury, brain oxygenation, and epileptic seizures after cardiac arrest. The results of this trial will be used to evaluate whether a larger RCT on this subject is justified.

**Trial registration:**

ClinicalTrials.gov, NCT02698917. Registered on 26 January 2016.

**Electronic supplementary material:**

The online version of this article (doi:10.1186/s13063-017-2257-0) contains supplementary material, which is available to authorized users.

## Background

Hypoxic ischemic encephalopathy is the leading cause of morbidity and mortality after out-of-hospital cardiac arrest (OHCA) [1]. The development of neurological injury occurs during the first 48 h after cardiac arrest, with cerebral hypoperfusion being a potential mechanism [2, 3]. The levels of arterial carbon dioxide tension (PaCO_2_), arterial oxygen tension (PaO_2_), and mean arterial pressure (MAP) may be modified during this period and this may influence cerebral blood flow (CBF), cerebral oxygen delivery, and potentially the severity of the developing brain injury. The optimal targets for PaCO_2_, PaO_2_, and MAP are currently undefined [4].

PaCO_2_ is a major determinant of CBF [5]. After the return of spontaneous circulation (ROSC), the autoregulation of CBF is impaired [6], but reactivity to changes in PaCO_2_ remains [7]. In addition to its role in regulating cerebral perfusion, CO_2_ may have anti-convulsive [8], anti-inflammatory, and anti-oxidant properties [9]. In animal models, moderate hypercapnia (PaCO_2_ 8.0–13.3 kPa) has been related to better neurological scores, less histological brain damage, and less apoptosis compared with normocapnia or severe hypercapnia after cerebral ischemia [10]. Observational studies in humans suggest that hypocapnia is associated with poor outcomes but that mild hypercapnia may be beneficial during the post-resuscitation period after cardiac arrest [11–13]. In the only randomized controlled trial (RCT) on this subject, the investigators compared mild hypercapnia (6.7–7.3 kPa) with normocapnia (4.5–6.0 kPa). The primary outcome was serum neuron-specific enolase (NSE) and S100b protein concentrations over the first 72 h. In this study, mild hypercapnia was associated with significantly lower NSE concentrations compared with normocapnia and no adverse effects were found to be related to higher PaCO_2_ levels [14]. However, hypoventilation and hypercapnia may aggravate acidosis, which is associated with poor neurological outcomes after cardiac arrest [15]. Moreover, in patients with severe acute respiratory distress syndrome (ARDS), acidosis and hypercapnia are associated with impaired right ventricular function and hemodynamic instability, which could impair the recovery of patients with post-cardiac arrest syndrome [16]. Thus far, all studies on this subject have compared hypocapnia and hypercapnia with normocapnia and there are no published data assessing the potential difference between high-normal and low-normal PaCO_2_ values, even though the normal range for PaCO_2_ values is relatively broad (4.5–6.0 kPa).

It has been suggested that exposure to high levels of PaO_2_ during the early stages of reperfusion after cardiac arrest may increase free radical production and thus exacerbate ischemia-reperfusion injury [17]. Retrospective cohort studies have found an association between severe hyperoxia (PaO_2_ > 40 kPa) and poor prognosis after cardiac arrest [18–21]. One observational study with frequent arterial blood gas (ABG) samples found that the combination of moderate hypercarbia and mild hyperoxia was associated with improved neurological recovery [12]. Another recent analysis of a high-resolution cardiac arrest database found that severe hyperoxia (PaO_2_ > 40 kPa) was associated with increased in-hospital mortality, while moderate hyperoxia (13.5–39.9 kPa) was correlated with improved organ function at 24 h after the return of spontaneous circulation (ROSC) [22]. In the only RCT on this subject, patients resuscitated from witnessed out-of-hospital ventricular fibrillation (VF) were randomized after the ROSC to be ventilated either with 30% or 100% oxygen for 60 min. Main outcome measures included NSE and S-100 protein concentrations at 24 and 48 h after ROSC, but unfortunately the study was not sufficiently powerful to show an effect on the brain injury markers [23]. Interventional studies are needed to determine the optimal oxygen concentration after cardiac arrest and the potential association between oxygen therapy and outcomes.

Arterial hypotension is common among patients resuscitated from cardiac arrest and it is associated with increased mortality [24]. Hemodynamic instability during the post-resuscitation period is thought to be caused by the severe, global ischemia-reperfusion injury associated with myocardial stunning [25], profound systemic inflammation [26], and adrenal axis suppression [27]. The autoregulation of CBF is disturbed and cerebral perfusion may become directly dependent on cerebral perfusion pressure (CPP), which is dependent on MAP [6]. The optimal MAP level after cardiac arrest is unknown and it is unclear whether the body’s intrinsic ability to maintain adequate perfusion pressure is just a predictor of good neurological recovery or whether supporting the circulation with vasoactive agents improves outcomes. In animal models, inducing hypertension with vasoactive agents during the post-resuscitation period has been related to less-severe brain injury and better neurological outcomes after asphyxial cardiac arrest [28]. In contrast, an observational human study of 168 patients found that vasoactive agent use in cases of post-cardiac arrest syndrome was associated with increased mortality and poor neurological outcomes [29]. According to another observational study, during the post-resuscitation period, MAP levels > 70 mmHg were associated with improved neurological outcomes, but if the patients needed vasopressor support to achieve this goal, there was no difference in recovery compared with patients with lower MAP levels and no use of vasopressors [30]. In a recent multi-center observational study that involved the high-frequency capture of MAP and vasopressor data, hypotension during the first 6 h after ICU admission was an independent predictor of worsened recovery after OHCA, but vasopressor load was not associated with poor outcomes [31]. RCTs are needed to evaluate whether interventions to support blood pressure improve neurological outcomes.

NSE is a cytoplasmic glycolytic enzyme specific to neurons and neuroectodermal cells. After neuronal damage, NSE is released into the cerebrospinal fluid and blood stream. Elevated or increasing levels during the first 24–72 h after cardiac arrest predict poor outcome [32, 33]. S100 is a neuroglial cell protein that is released into blood after cerebral damage and, as with NSE, elevated levels during the first 24–72 h after cardiac arrest predict poor outcome [32, 34]. Near-infrared spectroscopy (NIRS) is a non-invasive method to determine regional cerebral oxygen saturation (rSO_2_) and previous studies indicate its limited potential for early prediction of neurological outcome after cardiac arrest [3]. In the future, NIRS might be used as a continuous monitor to optimize cerebral perfusion and oxygenation after cardiac arrest, but further studies are needed. Changes in electroencephalogram (EEG) can also be used in prognostication after resuscitation. Presence of burst-suppression, status epilepticus, or poor reactivity on EEG after cardiac arrest and rewarming from therapeutic hypothermia are all related with poor neurological outcome [35].

According to current literature, high-normal PaCO_2_, PaO_2_, and MAP might contribute to lower levels of NSE and S100 and better neurological outcome after OHCA. With unconscious, mechanically ventilated patients, targeting specific levels of PaCO_2_, PaO_2_, and MAP should be feasible. The effect of different levels of PaCO_2_, PaO_2_, and MAP on NIRS and EEG during the post-resuscitation care is unknown. This article describes the study protocol for a prospective, multi-center, randomized pilot trial of targeting low- or high-normal carbon dioxide, oxygen, and mean arterial pressure after cardiac arrest and resuscitation (COMACARE).

## Methods/Design

The COMACARE trial is a prospective, multi-center, pilot RCT using 2^3^ factorial design. The main objectives of the study are to assess the feasibility of targeting low- or high-normal PaCO_2_, PaO_2_, and MAP in comatose, mechanically ventilated patients after OHCA and to evaluate the effect of low- or high-normal PaCO_2_, PaO_2_, and MAP on brain injury markers at 48 h after cardiac arrest. Secondary objectives are to assess the effect of low- or high-normal PaCO_2_, PaO_2_, and MAP after OHCA on cerebral oxygenation, epileptic activity, and neurological outcome six months after cardiac arrest. COMACARE is a RCT comparing multiple treatment groups with each other. There is no additional control group not receiving any study interventions. The trial is unblinded; due to the nature of the interventions, the treating personnel cannot be blinded regarding study group allocations.

### Outcomes

#### Primary outcome

NSE serum concentration at 48 h after cardiac arrest

#### Secondary outcomes

NSE serum concentration at 24 and 72 h after cardiac arrestS100 protein serum concentration at 24, 48, and 72 h after cardiac arrestCardiac troponin (TnT) concentration at 24, 48, and 72 h after cardiac arrestResults of NIRS monitoring during the first 48 h after admission to the ICUResults of continuous EEG monitoring for 48 h after arrival at the ICU and a statement of the findings by an experienced senior neurologist/neurophysiologistCerebral performance category (CPC) at six months after cardiac arrestTotal duration of intensive careTotal duration of mechanical ventilationLength of hospital stayDischarge destinationVital status at hospital discharge (dead or alive)

#### Feasibility outcomes

Difference in PaCO2 between groups targeting low-normal (4.5-4.7 kPa) and high-normal (5.8–6.0) PaCO_2_
Difference in PaO2 between groups targeting low-normal (10–15 kPa) and high-normal (20–25 kPa) PaO_2_
Difference in MAP between groups targeting low-normal (65–75 mmHg) and high-normal (80–100 mmHg) MAPDistribution of values for primary and secondary outcomesRandomized/screened patient ratioConsent rateData completion rateRecruitment duration

### Study setting and participants

Six intensive care units (ICUs) across Finland and one center in Denmark will participate in this trial. The participating Finnish hospitals are Helsinki University Hospital (Helsinki), Päijät-Häme Central Hospital (Lahti), Tampere University Hospital (Tampere), Central Finland Central Hospital (Jyväskylä), Kuopio University Hospital (Kuopio), and North Carelia Central Hospital (Joensuu). The Danish center is Aarhus University Hospital in Aarhus, Denmark. All patients admitted to one of the participating ICUs who experience ROSC after OHCA will be screened for eligibility.

### Inclusion criteria

Witnessed OHCA with VF or ventricular tachycardia (VT) as the initial rhythmROSC within 10–45 min from the start of arrestArrest has confirmed or suspected cardiac originMechanical ventilation upon arrival at ICUMarkedly impaired level of consciousness defined as no response to verbal commands and Glasgow Coma Scale (GCS) motor score < 5 (withdrawal to painful stimuli at best)Deferred consent possible or likely, or informed consent obtained, according to local ethical praxisActive intensive care initiated, including targeted temperature management (33–36 °C)

### Exclusion criteria

In-hospital cardiac arrestCardiac arrest with non-shockable initial rhythm (asystole or pulseless electrical activity)Arrest with a confirmed or presumed non-cardiac etiologyProbable withdrawal from active ICU care due to terminal illness or poor prognosis because of severely reduced functional status before cardiac arrestDeferred consent impossible or unlikely (no known next of kin or relatives)Conscious patient or only mild impairment of consciousness (responsive to verbal commands or GCS motor score ≥ 5)Confirmed or suspected acute or pre-existing intracranial pathology and/or suspicion of increased intracranial pressureAge < 18 or > 80 yearsPregnancySevere oxygenation disorder (PaO_2_/FiO_2_ < 100 mmHg)Severe chronic obstructive pulmonary disease (COPD)

### Randomization and intervention

Schedule of enrolment, interventions, and assessments of the COMACARE trial are presented in Fig. 1. After ICU admission, participants are randomized into one of eight arms, with each arm having a different combination of PaCO_2_, PaO_2_, and MAP targets according to the 2^3^ factorial design:Low-normal PaCO_2_ (4.5–4.7 kPa), low-normal PaO_2_ (10–15 kPa), low-normal MAP (65–75 mmHg);High-normal PaCO_2_ (5.8–6.0 kPa), low-normal PaO_2_ (10–15 kPa), low-normal MAP (65–75 mmHg);Low-normal PaCO_2_ (4.5–4.7 kPa), high-normal PaO_2_ (20–25 kPa), low-normal MAP (65–75 mmHg);High-normal PaCO_2_ (5.8–6.0 kPa), high-normal PaO_2_ (20–25 kPa), low-normal MAP (65–75 mmHg);Low-normal PaCO_2_ (4.5–4.7 kPa), low-normal PaO_2_ (10–15 kPa), high-normal MAP (80–100 mmHg);High-normal PaCO_2_ (5.8–6.0 kPa), low-normal PaO_2_ (10–15 kPa), high-normal MAP (80–100 mmHg);Low-normal PaCO_2_ (4.5–4.7 kPa), high-normal PaO_2_ (20–25 kPa), high-normal MAP (80–100 mmHg);High-normal PaCO_2_ (5.8–6 kPa), high-normal PaO_2_ (20–25 kPa), high-normal MAP (80–100 mmHg).

**Fig. 1 Fig1:**
[figure not shown]
Schedule of enrolment, interventions, and assessments of the COMACARE trial

Study centers will have access to a web-based randomization system. A cryptographically strong random number generator with modulo bias eliminated is used to generate random numbers and an unbiased Fisher-Yates (Durstenfeld) algorithm is used to shuffle blocks. Randomization is stratified with respect to target temperature (33 °C or 36 °C).

The treating clinicians and nurses will be made aware of treatment targets using laminated signs at the patient’s bedside and on mechanical ventilators (Fig. 2).

**Fig. 2 Fig2:**
[figure not shown]
Picture of the COMACARE treatment target card attached to a ventilator

Low-normal and high-normal carbon dioxide levels will be targeted by adjusting minute ventilation (tidal volume and frequency) based on the results of an ABG analysis (corrected to the patient’s actual temperature) and using the corresponding end-tidal carbon dioxide (EtCO_2_) value as an additional guide. Low-normal and high-normal PaO_2_ levels will be targeted by adjusting the fraction of inspired oxygen (FiO_2_) in the range of 21–100% and using moderate levels (8–10 cmH_2_O) of positive end-expiratory pressure (PEEP). Peripheral oxygen saturation (SpO_2_) can be used as an additional guide in the low-normal PaO_2_ group in order to avoid hypoxia and to remain within the target range. In the high-normal PaO_2_ group, SpO_2_ will be close to 100% and it cannot be used to monitor the oxygenation reliably. Arterial blood gas samples will be obtained at least every 3 h to ensure that blood gas levels are within the target ranges. Low-normal and high-normal MAP levels will be targeted by using a continuous infusion of noradrenaline as needed. Fluid boluses are allowed for the treatment of hypovolemia, according to the treating clinician’s preference. In cases of confirmed or suspected low cardiac output, the use of an inotrope, such as dobutamine or levosimendan, is allowed. There are no limits to the infusion rates of noradrenalin or inotropes and the dose will be determined according to local ICU protocols and the treating clinician’s preference. No efforts other than sedation and pain medication will be made to lower blood pressure levels in order to meet the low-normal target. In cases of hypertensive crisis (defined as MAP > 140 mmHg) or suspected or detected left ventricular systolic dysfunction, the blood pressure may be lowered using vasodilating agents, according to the treating clinician’s preference.

No further instructions of how to achieve the target levels of PaCO_2_, PaO_2_, and MAP will be given to the treating clinicians. The intervention will continue for 36 h or until the patient is extubated or ventilation is set to a spontaneous mode.

### Sample size

For the power analysis, we assumed that there is no interaction between PaCO_2_, PaO_2_, and MAP and considered each intervention independently. The primary endpoint will be the NSE value at 48 h from the arrest. Based on our previous cohort of OHCA patients, the mean NSE at 48 h is around 17 μg/L and the standard deviation is around 20 [36]. In a previous, small RCT, the use of 30% FiO_2_, compared with 100% FiO_2_, resulted in approximately 50% increase of NSE values at 48 h in the subset of patients treated with hypothermia [23]. Assuming this previous finding, a study with 39 patients in each arm would have a power of 80%, with the significance set at 0.05, to detect a 50% increase in NSE. Given the possibility of death prior to 48 h and loss of follow-up, we will include 50% more patients than the target. Therefore, a total of 120 patients will be included (60 patients in each intervention arm).

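### The claimed 80% power with 39 patients per level does not follow from the protocol's own mean, SD and effect, which give about 46% power and need about 88 per level

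*Protocol article*

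**What the plan says.** The Sample size section names the endpoint ("The primary endpoint will be the NSE value at 48 h from the arrest") and considers each of the three interventions separately, assuming no interaction. Each comparison is therefore between the two levels of one factor.

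From an earlier cohort of the investigators it states that "the mean NSE at 48 h is around 17" μg/L and that "the standard deviation is around 20". The effect comes from the hypothermia subset of a small earlier oxygen trial, and the aim is "to detect a 50% increase in NSE". The conclusion is that "a study with 39 patients in each arm would have a power of 80%, with the significance set at 0.05". Half as many patients again are added for early death and loss, which leads to 60 per level and 120 in all.

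The section gives no test, sidedness, transformation or distribution for this calculation. The Statistical analysis section plans a Mann-Whitney test for NSE at 48 h.

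**The concern.** The assumed SD is larger than the assumed mean, so a 50% change in the mean is less than half an SD. An effect of that size normally needs well over 39 patients per group for 80% power.

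NSE at 48 h is the named primary outcome, and the effect on brain injury markers is one of the main objectives. The Discussion section plans three papers and says that the results will inform whether a larger trial is justified. A reader who trusts the stated power would think that a true 50% effect is missed one time in five. On the stated inputs the t-test would miss it about 54% of the time (1 − 0.457) with 39 per level. A null result could then count against a larger trial when it says little either way.

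The size of the effect is also weakly supported. The Background section says of the trial that supplied the 50% that "the study was not sufficiently powerful to show an effect on the brain injury markers". The arithmetic below does not depend on this.

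**Working it through.** **Inputs (Sample size section).** Mean 17, SD 20, increase 50%, alpha 0.05, power 80%, equal groups. Sidedness is not stated; two-sided is taken as the default and one-sided is also tried.

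**Effect.** Difference = 0.5 × 17 = 8.5. Standardised difference = 8.5 / 20 = 0.425.

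**Attempt to reproduce 39.** By the normal approximation, n per level = 2 × (1.960 + 0.842)² × (20 / 8.5)² = 87. The exact two-sample t-test gives 87.9, so 88. The stated 39 is not reproduced.

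**Power at the stated numbers (two-sided).**

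| Evaluable per level | Normal approximation | t-test |
|---|---|---|
| 39 | 46.7% | 45.7% |
| 60 | 64.4% | 63.6% |

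**Inflation step.** 39 × 1.5 = 58.5, taken up to 60. This step is consistent; the fault lies in the 39. With 88 per level, the evaluable total would be 176, and the protocol's own allowance would make it 264 (88 × 2 × 1.5).

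**Other readings tried.**

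- One-sided test: n = 69 (normal) or 70 (t-test); power at 39 is 59%.
- Rounding of the approximate inputs (mean 16.5 to 17.5, SD 19.5 to 20.5): n = 78 to 97; power at 39 is 42% to 50%.
- Log scale: log-SD = √ln(1 + (20/17)²) = 0.932; effect = ln 1.5 / 0.932 = 0.435; n = 84 by t-test; power at 39 is about 48%.
- Mann-Whitney under the same log-normal model: 84 / 0.955 = 88 per level. Simulated power for a 1.5-fold effect is 45% at 39, 64% at 60 and 79% at 87.
- SD rising in proportion to the mean (20 and 30), analysed on the original scale: n = 142; power at 39 is 31%.
- 17 taken as the pooled mean (difference 6.8): n = 136. 17 taken as the mean of the higher group: n = 142 to 196.

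**What would give 39.** An SD of about 13.2 (t-test), a log-SD of about 0.63, or a difference of 12.75, which is 75% of 17. The section states none of these.

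**Increase detectable with 80% power (t-test, SD 20).** At 39 per level the difference needed is 12.85, and 12.85 / 17 = 76%. At 60 per level the increase is about 61%. On the log scale the corresponding ratios are 1.82 and 1.62.

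**The case against.** The strongest reply concerns the planned test. A positive concentration with mean 17 and SD 20 must be strongly skewed, and a rank test can do much better than a t-test on skewed data. If the SD is held at 20 in both groups with means 17 and 25.5, simulated Mann-Whitney power at 39 per level is 87% (log-normal) or 78% (gamma). A log-normal shifted by 8.5 gives 95%. The 45% figure for the same test rests on a multiplicative effect, which gives the higher group an SD of 30. A multiplicative effect on a gamma shape gives only 24%. Power under the planned test therefore depends heavily on assumptions that the article does not state, and 46% should be labelled as the t-test figure. That much stands.

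It does not rescue the stated claim. The section names no such distribution, and results from 24% to 95% do not derive 80% from the printed inputs. The log-normal case with equal SDs also enlarges the effect that a rank test sees. Its medians are 17 / √(1 + (20/17)²) = 11.0 and 25.5 / √(1 + (20/25.5)²) = 20.1, a ratio of about 1.82 rather than 1.5. On the log scale, 1.82 is the ratio that 39 per level can detect with 80% power.

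It can also be said that this is a pilot with feasibility as a joint aim, and that the cohort and trial behind the inputs are not shown. A pilot need not have 80% power, which limits the practical consequence, but a power that is stated must be right. If unreported inputs produced 39, they differ from those printed and need to be given.

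**Conclusion.** The concern holds. On the stated mean, SD, increase and significance level, 80% power needs about 88 evaluable patients per level, more than twice the stated 39. Power is about 46% with 39 and about 64% with all 60.

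These figures rest on a two-sided t-test with SD 20 in both groups. The log scale, and Mann-Whitney with a 1.5-fold log-normal effect, give nearly the same answer. Other skewed models move the power widely in both directions, but none of them is stated and none yields 39 from the printed inputs. The consequence is for the interpretation of the NSE result, not for the conduct of the trial.

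**What to change.** Keep 120 patients and correct the Sample size paragraph before results are published.

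- If other inputs produced 39 (for example an SD of about 13 or a log-SD of about 0.63), state them with their source, together with the test, sidedness and scale.
- Otherwise replace the power sentence with: *With mean 17, SD 20 and 39 evaluable patients per level, a two-sided t-test at 0.05 has about 46% power for a 50% increase in NSE (64% if all 60 per level are evaluable); 80% power is reached for an increase of about 76% (61%).*
- Add that power under the planned Mann-Whitney test depends on the shape of the NSE distribution, and is about 45% at 39 per level for a 1.5-fold log-normal effect.
- Add that a non-significant NSE comparison is inconclusive and will be reported as a ratio with its 95% confidence interval.

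The cost is wording and a less favourable power statement. Recruitment stood at 115 of 120, and no extra patients are needed.
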